### The study will be suspended early or terminated if any of the following occur:

Serious adverse event (SAE)The efficacy of the test drug is found to be poor or even ineffectiveFlawed protocol or significant deviation from the well-designed protocolThe pharmaceutical supervisory and administrative department decides to terminate the study for any reasonThe sponsor decides to terminate the trial due to management or funding problems

### Interventions

Gantong Granules and placebo are provided and manufactured by Beikelian Pharmaceutical & Technology Co., Ltd, Shenzhen, China. Considering the characteristics of Chinese herbal medicine, placebo is prepared by 10-fold dilution of 5 g of Gantong Granules and then condensed into granules. The minimum effective dose of Gantong Granules is 5 g. After 10-fold dilution, the placebo will not have any clinical or pharmacological effects. Placebo is almost identical to the test drug in appearance, smell and taste. This preparation of placebo has been used in herbal medicine trials in China and Japan. All drugs are concealed in uniform packages with the same labels and each package contains 5 plus 1 days’ dosage. Patients in the high-dose group, medium-dose group, low-dose group or placebo control group, will receive Gantong Granules 15 g, Gantong Granules 10 g plus placebo 5 g, Gantong Granules 5 g plus placebo 10 g or placebo 15 g, respectively. All drugs will be dissolved in 200 ml warm water and taken orally before each meal 3 times daily for 3 to 5 days. If all symptoms disappear within 3 days, the study drugs should be taken for just 3 days; if not, for 5 days. During the study, patients will be visited five times by the investigators. The follow-up visits last for 7 days after the treatment. Details of study procedures are shown in Figure 2.

**Figure 2 Fig2:**
[figure not shown]
Study schedule for patients.

### Concomitant treatments and forbidden drugs

Patients will be allowed to continue using medications for comorbidities, such as hypertension or diabetes. The dosage, duration and name of any concomitant medication or treatment must be recorded carefully in the case report form (CRF). When the body temperature of a participant rises to higher than 39.0°C, physical cooling and/or paracetamol can be used to reduce the fever. Any other Western or Chinese therapy or medication that may affect the study results is prohibited during the trial.

### Outcome measures

#### Primary outcomes

The primary outcome of the study is the duration of all symptoms, which is defined as the number of hours from study enrollment to the time when the patient’s illness symptoms completely resolve. Each participant will be instructed to record any changes in symptoms in the patient diary, in which the data can be acquired. Investigator will make an assessment of the duration based on these data.

#### Secondary outcomes

Secondary outcomes include duration of primary symptoms and each symptom, time to fever relief and time to fever clearance, change in TCM symptom score, and change in Symptom and Sign Score.

### Time to fever relief and time to fever clearance

In this study, all patients will be asked to record their axillary temperature in the patient diary every 2 hours within the first 24 hours; after that, if the temperature is equal to or higher than 37.3°C, it should be recorded every 4 hours, and if the temperature is lower than 37.3°C, then it should be recorded at 8 am. and 4 pm. every day. If the temperature is below 37.3°C and no longer rises for 48 hours, subjects do not need to continue recording. Time to fever relief is defined as the time from the first dose of the study drug until the body temperature drops 0.5°C or to normal; time to fever clearance is defined as the time from the first dose of the study drug until the body temperature drops below 37.3°C and no longer rises for 48 hours(calculated as the time to the start of the 48-hour period).

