**Table 1 Tab1:** **Traditional Chinese Medicine (TCM) diagnostic criteria**

**Category**	**Symptoms and signs**
Primary symptoms	Fever, mild aversion to cold, sore throat
Secondary symptoms	Sore limbs, nasal congestion, nasal discharge, thirsty, cough
Signs for the tongue	Red tongue and thin yellow tongue coating
Signs for the pulse	Floating and rapid pulse

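### After the first 24 hours, twice-daily daytime readings cannot verify the 48-hour no-rise condition of fever clearance, so clearance can be dated too early

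*Protocol article*

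**What the plan says.** The section on time to fever relief and time to fever clearance sets the diary schedule in three steps.

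- At the start, patients "record their axillary temperature in the patient diary every 2 hours within the first 24 hours", whatever the temperature.
- After that, "if the temperature is equal to or higher than 37.3°C, it should be recorded every 4 hours".
- Otherwise, "if the temperature is lower than 37.3°C, then it should be recorded at 8 am. and 4 pm. every day".

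Recording may then end: "If the temperature is below 37.3°C and no longer rises for 48 hours, subjects do not need to continue recording".

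Fever clearance runs from the first dose "until the body temperature drops below 37.3°C and no longer rises for 48 hours", and it is "calculated as the time to the start of the 48-hour period".

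Two other places matter for how far the point reaches. Table 1 lists the primary symptoms as "Fever, mild aversion to cold, sore throat". The primary outcome is "the number of hours from study enrollment to the time when the patient’s illness symptoms completely resolve"; it comes from a diary in which patients note any symptom change, followed by an investigator's assessment.

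**The concern.** The definition of clearance asks for evidence about a continuous 48 hours. From the second day on, the schedule supplies that evidence only at two daytime points, 8 hours apart, and leaves the other 16 hours of each day unread. A fall in temperature is looked for every 4 hours; a later rise may go 16 hours without a reading.

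The error has one direction. Clearance is back-dated to the start of the window, so a rise that nobody records leaves the clearance time where it was, when it should have moved later. Missed rises can shorten time to fever clearance and cannot lengthen it. At stake is whether this named secondary outcome measures sustained clearance or only two daytime readings on each of two days.

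**Working it through.** The protocol article gives no figure for the performance of this schedule, so there is none to reproduce. The inputs are the reading times and the 48-hour rule quoted above. I read a rise as a return to 37.3°C or more, and I assume that no reading is taken outside the schedule.

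**Readings in a confirmation window**

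- 08:00 and 16:00 only: 48 h × 2 readings per 24 h = 4 readings, whatever the start time. The unread nights total 2 × 16 h = 32 h of the 48 h.
- 4-hourly: 48 / 4 = 12 readings.
- A window that starts in the first 24 hours is denser. With a fall at hour 12, six more 2-hourly readings follow (hours 14 to 24), then about three twice-daily readings over the remaining 36 h, so about nine in all.

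**Chance of missing one episode**

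Assume one fever episode of d hours whose onset is uniform over the 24 h. It is missed if it lies wholly inside a gap between readings, so P(miss) is the sum over gaps g of max(0, g − d), divided by 24.

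- 08:00 and 16:00: gaps of 8 h and 16 h.
  - d = 4: (4 + 12)/24 = 67%
  - d = 6: (2 + 10)/24 = 50%
  - d = 8: (0 + 8)/24 = 33%
  - d = 12: (0 + 4)/24 = 17%
- 4-hourly round the clock: max(0, 4 − d)/4 = 0% for every d of 4 h or more.
- 08:00, 16:00 and 20:00: gaps of 8 h, 4 h and 12 h.
  - d = 4: (4 + 0 + 8)/24 = 50%
  - d = 6: (2 + 0 + 6)/24 = 33%
  - d = 8: (0 + 0 + 4)/24 = 17%

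An episode from 18:00 to 24:00 is always missed by the 08:00 and 16:00 readings, and always caught once 20:00 is added.

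**Size of the dating error**

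Take a patient past the first 24 hours who has unseen fever from 18:00 to 24:00. The error is the time from the first low reading to the end of the last unseen fever.

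- First low reading at 16:00, one evening: 24 − 16 = 8 h.
- First low reading at 08:00, one evening: 24 − 8 = 16 h.
- First low reading at 08:00, two evenings: 16 + 24 = 40 h.

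For scale only, the sample size section treats 2 days (48 h) as the relevant difference, but for the duration of all symptoms and not for fever clearance.

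**The case against.** The strongest reply is that fewer self-readings once a patient is afebrile is a reasonable trade against burden. Nothing in the article suggests that brief, isolated night fever is common, and entry is limited to a temperature of at most 38.5°C. It is true that the frequency is unknown, so the size of the problem in practice is unknown too. The mismatch between a 48-hour condition and a schedule with 16-hour gaps remains.

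A reader might also infer several stronger points, which the document does not support.

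- **Early fallers are watched least.** The first 24 hours are read 2-hourly at any temperature. A patient whose fever falls at hour 12 gets about nine confirmatory readings; one who first falls after day 1 gets four.
- **The faster-acting arm is favoured.** All arms follow the same schedule under blinding. A bias between arms would need unseen rises to differ by arm, and the article gives no information on that. It is possible, not shown.
- **Ending the readings after 48 hours makes clearance too early.** A true 48 hours without a rise is exactly what the definition asks for. Stopping does harm to this outcome only if those 48 hours were wrongly judged free of fever. Stopping is also optional, and the safety outcomes section requires a temperature after treatment, so measurement does not end there.
- **The primary outcome is dated too early.** It rests on a diary of any symptom change, and the text does not tie it to the temperature schedule. A fever that the patient feels in the evening can be written down. Early dating would need a fever that was not felt or not recorded, and fever as the last symptom to resolve.
- **Every missed rise costs a day or more.** The illustrated errors run from 8 h to 40 h.

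**Conclusion.** The point holds for time to fever clearance. After the first 24 hours, the scheduled readings cannot verify the 48-hour condition, and an unseen evening or night rise can date clearance too early: by 8, 16 or 40 h in the three illustrated cases.

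The miss chances of 67%, 50% and 33% for episodes of 4, 6 and 8 h rest on a uniformly random onset and on no reading outside the schedule. They apply to an episode that occurs; they do not say how many patients have one. Effects on the duration of fever as a symptom and on the primary outcome are possible but limited. The sample size is not affected. This is a modest weakness in one secondary outcome, worth mending because the remedy is cheap.

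**What to change.** Until the 48-hour confirmation window is complete, keep 4-hourly readings while the patient is awake, or at least add one fixed evening reading (for example 20:00) to those at 08:00 and 16:00. Add a reading whenever the patient feels feverish, and state that any reading of 37.3°C or more restarts the 48 hours.

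The 20:00 reading alone lowers the miss chance to 50%, 33% and 17% for episodes of 4, 6 and 8 h. It does not close the night, since 12 h remain unread, but it covers the evening.

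The trial status section says that recruitment is under way, so the change should come into force for all arms from a dated amendment. The cost is protocol and diary wording and a few more self-taken readings per patient, with no extra visit or equipment. Some clearance times will become longer.

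### Time to fever relief can be met by a temperature fall that follows permitted paracetamol or cooling, because the definition has no rescue condition and no reference temperature

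*Protocol article*

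**What the plan says.** The section on time to fever relief and time to fever clearance gives both definitions. For relief: "Time to fever relief is defined as the time from the first dose of the study drug until the body temperature drops 0.5°C or to" a normal value. For clearance, the clock also starts at the first dose and runs "until the body temperature drops below 37.3°C and no longer rises for 48 hours", with the event dated to the start of that period. In the first 24 hours, patients record axillary temperature every 2 hours.

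The section on concomitant treatments and forbidden drugs states: "When the body temperature of a participant rises to higher than 39.0°C, physical cooling and/or paracetamol can be used to reduce the fever". It adds "Any other Western or Chinese therapy or medication that may affect the study results is prohibited during the trial". On documentation it says "The dosage, duration and name of any concomitant medication or treatment must be recorded carefully in the case report form (CRF").

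Three other places bear on the point. The exclusion criteria bar entry above 38.5°C. The withdrawal criteria list a temperature above 39.0°C as an example of worsening. The fever measures are secondary outcomes ("time to fever relief and time to fever clearance, change in TCM symptom score, and change in Symptom and Sign Score"), and the statistical analysis section assigns them Kaplan-Meier estimation and a stratified log-rank test, with the full analysis set primary under the intention-to-treat principle.

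**The concern.** Rescue is given in order to lower temperature, and a lowered temperature is the event. Nothing in the relief definition separates a fall under study drug alone from a fall after paracetamol or cooling. Relief needs no persistence, so one low reading while the antipyretic is acting is enough, and 2-hourly readings make it likely that such a reading is caught.

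The patients concerned are those doing worst, since they have gone above 39.0°C. Scoring them as relieved soon after rescue turns some of the longest relief times into short ones. If the drug lowers fever, more placebo patients would be expected to need rescue, and the distortion would then work against the active arms and flatten the dose comparison that the trial is meant to inform.

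**Working it through.** **1. The plan's own figure.** No figure is given for the fever endpoints. The sample size concerns the primary outcome and reproduces: 2 × (1.96 + 1.2816)² × 3²/2² = 47.3, so 48 per group; 48/0.8 = 60; 4 × 60 = 240. It says nothing about this point.

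**2. Who can be affected.** Entry is at most 38.5°C and rescue begins above 39.0°C, so a rescued patient has risen by more than 0.5°C since entry. Only those who worsen this far before meeting relief matter.

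**3. The missing reference temperature.** Take an invented patient who enters at 38.3°C, reaches 39.1°C, is rescued and then reads 38.4°C.
- Measured from the peak: 39.1 − 38.4 = 0.7°C, so relief is scored although the patient is hotter than at entry.
- Measured from entry: relief needs 38.3 − 0.5 = 37.8°C, so 38.4°C is not relief.

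Even from entry, rescue can still produce the event, but it needs a larger fall. A patient who entered at 38.5°C must drop from above 39.0°C to 38.0°C, that is, by more than 1.0°C.

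**4. Illustration of size.** All inputs here are assumptions: exponential relief times with median m = 24 h on placebo and 16 h on active; rescue falling on patients slower than their arm's median; rescue time uniform from 2 h to m; relief scored 2 h after every rescue.

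True mean: μ = m/ln 2, which is 34.62 h and 23.08 h (ratio 1.50). A slower-than-median patient has mean m + μ, which is 58.62 h and 39.08 h. A rescued patient's recorded mean is (2 + m)/2 + 2, which is 15 h and 11 h. With a fraction r rescued, the recorded mean is μ − r × 43.62 on placebo (58.62 − 15) and μ − r × 28.08 on active (39.08 − 11).

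| Rescued, placebo/active | Placebo mean (h) | Active mean (h) | Difference (h) | Ratio |
|---|---|---|---|---|
| 0% / 0% | 34.62 | 23.08 | 11.54 | 1.50 |
| 5% / 2% | 32.44 | 22.52 | 9.92 | 1.44 |
| 10% / 5% | 30.26 | 21.68 | 8.58 | 1.40 |
| 20% / 10% | 25.90 | 20.27 | 5.63 | 1.28 |

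A simulation of 400,000 patients per arm with censoring at 120 h gives rate ratios of 1.44, 1.39 and 1.27, in line with the table.

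If only half of rescues reach the threshold, the ratios are about 1.47, 1.45 and 1.39. With a quarter they are about 1.48, 1.47 and 1.45. With 20% rescued in both arms and every rescue counted, (34.62 − 8.72)/(23.08 − 5.62) = 1.48, so in this model the shift in the ratio comes almost wholly from unequal rescue.

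**5. A second model, in terms of power.** This used 60 v 60 patients, an unstratified log-rank test, 3,000 runs, the same medians, and rescue at a uniform time in the first 24 h if the patient was not yet relieved. Power without rescue is about 0.58.

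| Rescued, placebo/active | Rescue fall scored as relief | Censored at rescue | Not relieved to 120 h |
|---|---|---|---|
| 4% / 1% | 0.52 | 0.57 | 0.60 |
| 7% / 3% | 0.46 | 0.55 | 0.60 |
| 14% / 6% | 0.36 | 0.54 | 0.64 |
| 29% / 13% | 0.16 | 0.48 | 0.74 |

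In this model near-equal rescue (14.5% v 12.4%) also costs power, 0.47 against about 0.60, so imbalance is not the only route to dilution.

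**The case against.** The case on the other side has real force.

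- **The definition does not count just any fall.** Relief needs 0.5°C or normal, and rescue is confined to temperatures above 39.0°C. This stands and limits the point to patients who worsen before relief.
- **Timing from first dose suggests a first-dose reference, under which many rescue falls would not qualify.** This is a natural reading, but the text does not state it, and even on that reading a large enough rescue fall counts.
- **Clearance protects itself.** This largely stands. Rescue cannot be given while the temperature stays below 37.3°C, and a returning fever breaks the 48-hour period. At most, a rescue just before the period could move its start.
- **A reader might infer that the primary outcome is biased too.** The documents do not support that. It is "the number of hours from study enrollment to the time when the patient’s illness symptoms completely resolve", and the symptoms include nasal congestion, nasal discharge and cough, which a short antipyretic effect would seldom bring to an end.
- **Patients above 39.0°C may be withdrawn.** If so, their later readings may never be scored, and the problem becomes informative censoring, with a smaller loss of about 1 to 10 power points in the illustration. This stands as a reason to reconcile the sections. It does not cure the definition, because the rescue provision speaks of participants and the analysis follows intention to treat.
- **Counting outcomes regardless of rescue is a recognised treatment-policy choice, and such rules often sit in the analysis plan.** The analysis plan may indeed add a rule. But the article fixes the threshold, clock start, reading schedule and back-dating of this endpoint, and so defined it can credit an antipyretic's effect to the study drug. The data section places the plan at the blind review, when it is too late to capture rescue times that were not recorded.

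**Conclusion.** The point holds for time to fever relief. As worded, a rescue-induced fall can be scored as relief, and if rescue is commoner on placebo the comparison moves toward no difference. That placebo patients would need more rescue is an inference from the drug working; no figure in the documents shows it. Nor is there any basis for saying that the rule hides harm from a dose.

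The size is unknown. The fall from 1.50 to between 1.44 and 1.27 rests on assumed medians, assumed rescue rates, and every rescue succeeding; with a quarter succeeding it is about 1.48 to 1.45. Clearance is much less exposed, and no effect on the primary outcome is shown. The endpoint is secondary, so this is a change that should be made, not one that threatens the trial's main conclusion.

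**What to change.** In the endpoint definition:
- Measure the 0.5°C fall from the temperature before the first dose.
- Do not count as relief a fall first seen within a pre-specified interval after an antipyretic or physical cooling. A rescued patient stays not relieved until readings outside that interval qualify.
- Start the 48-hour clearance period only from readings outside that interval.

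In data collection, record the time of each rescue in the diary or case report form; the items now listed do not include it.

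In the analysis, add a sensitivity analysis with rescued patients held as not relieved to the end of observation, and report rescue by arm. That analysis is not neutral: in the illustration it raises power to as much as 0.74 when placebo is rescued more often. It should therefore stand beside the main result and not replace it.

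The withdrawal criterion and the rescue provision, both at 39.0°C, must be reconciled so that it is clear whether these patients' later readings are analysed. No clinical rule is proposed here.

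The cost is wording, one diary or form item and one extra analysis, with no additional patients or visits. A few rescued patients will get later or censored event times.

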### Change in TCM symptom score

The TCM symptom score system used in the study follows the *Guidelines for Clinical Research of New Chinese Medicine* [19], in which all symptoms are given graded scores (Figure 3). TCM signs will also be assessed, but not scored. The sum of all symptom scores is the cumulative TCM symptom score. The change in cumulative TCM symptom score is assessed by the percentage of symptom score reduction (PSSR), which is calculated according to the following formula:$$ \mathrm{PSSR}\kern0.5em =\kern0.6em \left(\frac{symptom\  score\  before\  treatment\hbox{-} symptom\  score\  after\  treatment}{symptom\  score\  before\  treatment}\right)\kern0.5em \times \kern0.5em 100\% $$

**Figure 3 Fig3:**
[figure not shown]
Symptom and Sign Scoring system.

### Change in Symptom and Sign Score

Pharyngeal hyperemia will be given graded scores as common cold sign (Figure 3). The change in cumulative Symptom and Sign Score is evaluated by the percentage of Symptom and Sign Score reduction (PSSSR), which is calculated according to the following formula:$$ \mathrm{PSSSR}\kern0.5em =\kern0.5em \left(\frac{symptom\  and\  sign\  score\  before\  treatment\hbox{-} symptom\  and\  sign\  score\  after\  treatment}{symptom\  and\  sign\  score\  before\  treatment}\right)\kern0.5em \times \kern0.5em 100\% $$

### Safety outcomes

Physical examination and some laboratory tests will be performed both before and after treatment for safety assessment. Physical examination includes temperature, respiration, blood pressure, heart rate and weight. Laboratory tests include routine blood test, urine analysis, liver function test (ALT, AST, ALP, STB, and γ-GT), renal function test (serum creatinine, microalbuminuria, and serum cystatin C), and electrocardiogram. Beyond that, before treatment, all subjects need to undergo a chest X-ray, and female patients of childbearing age need to take a urine pregnancy test.

### Adverse event reporting

It is very important to ensure all patients’ safety during the trial. Adverse events (AEs) should be recorded in detail on the adverse event form (AEF). All patients experiencing an AE will be treated appropriately. Regarding a SAE, the investigator must record it on the SAE form, and it should be reported to the principal investigator, CFDA, ethics committees and the sponsor within 24 hours.

### Quality control

All investigators are appropriately qualified by training and experience to conduct and supervise the trial. The principal investigator in each center will be responsible for the implementation of the clinical trial which should be in compliance with standard operation procedure. Throughout this trial, specialized quality inspectors will regularly review and monitor the experimental data from CRFs every week. Monitoring results should be presented to the principal investigator. The inspector will protect the privacy of the participants.

